**Usual care:**

The purposes of the usual care (UC) group are to provide (1) a task specific-based intervention that does not include use of visual cues to influence quality or adaptability of gait (2) an equal number of interactions and time spent with a physical therapist to minimize any potential for bias due to differential exposure and minimize the risk for differential loss to follow-up, and (3) a credible training program so that the participants would consider themselves involved in meaningful therapy activity.

Frequency and Duration: To match the VCT group, the UC group attends 16 therapy visits (2 times per week for 8 weeks) with length of control and VCT group training sessions the same. In these ways, the UC intervention will plausibly control for Hawthorne effect but exclusively through interventions that do not include visual cues.

Intensity: The intensity of exercise in the usual care group will be matched to the VCT group. The target exercise capacity is 20 minutes of continuous, independent, good stepping (as defined previously). In order to contrast intensity between VCT and UC groups a pedometer will be worn during training sessions to record the number of steps taken in each condition.

Goal setting and progression:

Participants may be asked to identify their primary walking goal, i.e. "I want to walk my dog in the park", "I want to be able to walk on busy walkways e.g. busy shopping centres". At each training session, specific training goals are reviewed with the participant and in the context of achieving the participant's goal. As the participant's skills progress during the training, the therapists also ask the participant, "what is limiting you from achieving your goal relative to walking?". Therapists may use the response to tailor the goals and parameters of the training session.

Content:

The therapist and participant identify daily activities that support the overall goals of walking to be incorporated on a daily basis at home or in the clinic. Participants will receive any prescribed usual care during the intervention period, because participants may be inhibited from enrolling in the study if they believe therapy opportunities will be reduced by enrolling. Usual care may include practice of: walking overground or on a treadmill and/or components of gait (such as weight shifting or intitation), and/or exercises aimed at improving upper or lower extremity strength, balance and coordination, and/or prescription of assistive devices (such as orthotics or walking aides). Patients will be required to abstain from any prescribed care that involves the use of visual cues for walking in therapy. Typical feedback would include therapist demonstrations of how the patient should correct their gait or physical guidance during walking. Therapists will keep a log of the exercises performed in the overground practice intervention delivered within the trial using a tick box form (Appendix 9).

*Self report logs*

The purpose of the Self Report Log (Appendix 10) is to track the amount of physical and occupational therapy participants receive during enrolment in the trial from *outside* sources. Participants, from both treatment groups, are instructed to write in the time (in minutes) of occupational or physical therapy they receive outside of their participation in the clinical trial on monthly calendars provided for them. They turn in a monthly calendar to the intervention therapist during the intervention period indicating any additional physical or occupational therapy during that time. Participants turn in a calendar monthly, even if no occupational or physical therapy was received.

The PI and co-PIs are responsible for maintaining standardization and competency throughout the trial. Communication between site lead therapists, PI and co-PIs is maintained through weekly conference calls. Pertinent aspects of the VCT and overground practice interventions are highlighted and discussed on conference calls to maintain consistency in decision making and progression. Email communication of specific questions regarding intervention delivery provides timely responses to questions from the therapy teams with responses available to all therapy personnel. A list of questions and responses is recorded throughout the trial and used to refine or clarify the training manual. PI conducts bi-monthly visits to each site and relays any intervention-related concerns to the Co-PIs.

Finally, the investigators have prepared an intervention training manual provided to all therapists. In addition, all participants received a participant Manual specific to either the VCT or overground training intervention to inform them of what to expect, goal-setting, progression across the sessions, and the role of the participant and therapists throughout the training.

### Criteria for terminating trial

Termination of the trial as a whole may be the result of poor recruitment or safety concerns should falls or other AEs be heavily prevalent in either treatment arm. However, the treatment is considered to be low risk and termination of the trial due to AEs is not anticipated.

**STATISTICS**

**METHODS**

### Statistical analysis

Demographic and other baseline data will be summarised by descriptive statistics (number[n], mean, standard deviation [SD], median, minimum and maximum) or frequency tables, stratified by treatment.

Measures of compliance will be summarised by descriptive statistics (number[n], mean, standard deviation [SD], median, minimum and maximum) or frequency tables, stratified by treatment.

Also calculation of the difference in proportions between the two treatments will be conducted to achieve meaningful clinically important difference.

No formal testing will be conducted since this is a pilot study to determine answers to questions for the definitive trial. Also no interim analysis will be conducted.

Further details of the statistical analysis will be supplied in the Statistical Analysis Plan (SAP), to be finalised in a seperate document.

All analysis will be performed using Stata 11, or above.

### SAMPLE SIZE AND JUSTIFICATION

This is a pilot study, with sample size being resource driven in terms of available subjects in a reasonable time frame, for which no formal statistically based sample size estimate is applicable.

For this pilot study, 50 patients from 5 recruitment sites will allow us to sample around 15 therapists and measure the recruitment rate from each site; n=50 will also give a reasonable estimate of acceptability and completeness of outcome data.

### ASSESSMENT OF EFFICACY

No assessment of efficacy will be performed since this is a pilot study designed primarily for assessing the feasibility of conducting a larger study.

### ASSESSMENT OF SAFETY

No special safety assessments are planned. Any serious adverse events will be reported to the study coordinating centre and then quarterly to the Trial Steering & Data Monitoring and Ethics Committees (TSC& DMEC).

### PROCEDURES FOR MISSING, UNUSED AND SPURIOUS DATA

Every effort will be made to reduce the proportion of missing data items through trial quality assurance procedures.

In terms of the dealing with any missing data we believe that imputation will not be appropriate for this case since as mentioned before this is a pilot study designed to obtain answers for a definite trial. Hence a tabulation of missing data and looking for reasons of any missing data will be a better method for this study. Using this information it will be possible to see what the majority of the missing data is (if any) and can then look for alternative procedures to minimise this further for the definitive trial.

### DEFINITION OF POPULATION ANALYSED

**Full analysis set:** All randomised participants who participated in at least one treatment and for whom at least one post-baseline assessment of the primary endpoint is available.

Primary and Secondary endpoints will be analysed using the full analysis set, defined as all randomised participants for whom a post-baseline assessment of the primary endpoint is available, that is, in accordance with the ‘intention to treat’ (ITT) principle.

This pilot study is designed to assess the feasibility of conducting a large scale trial and so no safety summaries will be necessary to be performed.

No per protocol analysis is envisaged therefore no assessment of protocol deviations will be performed.

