| Outcome measures | Primary outcome measure:  Proportion of participants achieiving a gait speed of 0.4 m/s and 0.8 m/s. Gait speed will be measured during a 10 metre walk.  2.Time and number of steps to complete a 90 degree turn.  number of steps taken to turn and time taken to turn in addition to step widths and lengths during turning. The number of times participants fail to hit stepping targets when these are presented unpredictably in timing and location will be used to indicate the ability to adapt the straight gait pattern according to environmental demands.  Secondary outcome measures:  3.Timed up and Go (TUG) test.  4.Fugl-Meyer Assessment will be used to assess changes in motor and sensory impairment.  5.Berg Balance Scale  6.A scale to assess mobility of people living in the community after stroke in different settings:  8. Falls Efficacy Scale to assess changes in confidence in functional mobility tasks.  8.SF-12 . This is a short-form health survey with only 12 questions. It yields an 8-scale profile of functional health and well-being scores, including physical functioning, and social, emotional, mental and general health and has been included to measure effects on broader quality of life. |
| Statistical methods | This is a pilot study to determine answers to questions for the definitive trial so there will be no formal statistical testing. We will tabulate the number and percentage of patients who are invited to participate, and who are recruited, into each arm of the trial. We will also tabulate the % of therapists willing to recruit patients into each arm of the trial, and the percentage of patients with complete outcome data (with 95% confidence limits). We will also estimate the difference in proportions achieving the meaningful clinically important difference (with 95% confidence limits). |

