### Primary endpoint

To achieve the stated aims, we will: a) Determine the numbers of patients willing to be recruited into both control and VCT groups; b) Determine the willingness of physiotherapists at each collaborating site to enrol patients to both control and VCT groups; c) Determine the numbers of patients who do not complete the allocated treatment, thus dropping out of the study; d) determine the reasons for dropping out; e) Measure completeness of outcome data, i.e. percentage of patients with no missing values in outcome assessments. In order to measure completeness of outcome data, the primary and secondary outcome measures that we proposed to use in the future definitive trial will be carried out as follows :

Primary outcome measures for walking and adaptability of walking respectively:

1. *Proportion of participants achieiving a gait speed of 0.4 m/s and 0.8 m/s*. Gait speed will be measured during a 10 metre walk. Participants will be given a 3 meter warm-up distance and 3 metres to walk beyond the 10 metres, and will walk at their usual pace. The time taken to walk the 10 metres will be recorded. Perry et al ([1995](#_ENREF_35))have shown that these gait speed classifications correspond to walking abilities in the community, with a gait speed of < 0.4 m/s for household walkers, of 0.4 – 0.8 m/s for limited community walkers, and >0.8 m/s for community walkers. It has been demonstrated that progressing from one of these classifications to the next correlates with improvement in physical functioning and quality of life([Schmid, Duncan et al. 2007](#_ENREF_40)) and these categories also correspond with changes in the Functional Ambulation Category, a categorical scale, rating level of skill in functional ambulation([Holden, Gill et al. 1986](#_ENREF_21)).

2.*Measures of adaptability of gait*: Time and number of steps to complete a 90 degree turn & the number of failures to hit targets presented unpredictably in timing and location.

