1. We have carried out a risk / benefit analysis of the all aspects for the study and found that overall the study is a low risk study. The only aspects of the study that raised a medium level of risk were:
   1. An increased risk of falling outside the house. We will specifically record this adverse event in the group who receive both the experimental and control interventions. The level of falls can be easily assessed by the TSC and a decision made regarding participant ethical and safety concerns.
   2. Implementation of the treatment - obtaining agreement from the PCTs to fund the treatment could be difficult, participants may not then receive the experimental intervention as planned
   3. Maintaining blinding (The research assistant will be blind to treatment allocation. However, as they are required to visit participants to complete the assessments, the participant may discuss what has been happening and therefore un-blind the research assistant). We will monitor this effect
   4. Collection of identifiable data for the Medical Research Information Services. We will be using this system to check if a participant is alive before we send any questionnaires. We will follow Research Governance procedures when collecting this information.
   5. Incomplete data, especially from questionnaires. We are using a Clinical trial Unit to collect and store data and to check weekly for incomplete data. We have a policy for increasing the rate of completion that will be followed
2. The pace of recruitment is anticipated to be very swift. If this is the case then the timescale to analyse the data and adjudicate as to proven effectiveness or otherwise of the intervention would mean that most, if not all, participants would already have been recruited by the time such a decision was reached.

[name] (University of Salford) has agreed to be the independent chair of the TSC & DMEC. We have also enrolled [name] (for independent scientific expertise on visual cueing and locomotor control) [name] as a patient representative and [name] (Senior Statistician, University of Glasgow as independent statistician), along with [name] (PI).

Schedule of meetings:

During the first work package fortnightly project meetings involving the grant holders will take place to manage the development phase. Three meetings will be scheduled to form the treatment manuals.

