### Removal of participants from therapy or assessments

Participants may permanently discontinue treatment if safety is considered to be at risk e.g. development of comorbidities preventing ability to participate in the treatment, the participant fails to comply with treatment or they withdraw consent. In all of these situations outcome data will continue to be sought at the usual planned time points when the participant and safety permits. Measures will be taken within 5 days following consent and treatment or they will not be included in the dataset at that time point. Given the aims of the study are to determine the numbers of patients who do not complete the allocated treatment, thus dropping out of the study, and determine the reasons for dropping out, withdrawn participants will not be replaced.

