### Participant removal from the study due to adverse events

Participants will be removed from the study following an AE if treating medical team indicate that the participant is no longer able to tolerate walking practice.

#

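### Read literally, the full analysis set removes participants with no post-baseline assessment before drop-out and data completeness, which are primary endpoints, are computed

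*Protocol*

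**What the plan says.** In the Protocol, Definition of population analysed, the full analysis set is defined twice.

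- First definition: "All randomised participants who participated in at least one treatment and for whom at least one post-baseline assessment of the primary endpoint is available".
- Second definition, in the next paragraph: "Primary and Secondary endpoints will be analysed using the full analysis set, defined as all randomised participants for whom a post-baseline assessment" exists for the primary endpoint. There is no treatment condition here. The sentence adds that this is "in accordance with the ‘intention to treat’ (ITT) principle".

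The section headed Primary endpoint opens with five feasibility items. Item (c) is "Determine the numbers of patients who do not complete the allocated treatment, thus dropping out of the study", item (d) is the reasons for dropping out, and item (e) is the percentage of patients with no missing outcome values. The gait and turning measures follow in the same section, as the means of measuring completeness. Primary objective repeats the feasibility items and says that drop-out rates will help to size the definitive trial.

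The Protocol says three things about people who leave treatment. Item (c) treats not completing treatment as leaving the study. Removal of participants from therapy or assessments says of permanent discontinuation: "In all of these situations outcome data will continue to be sought at the usual planned time points", as far as the participant and safety allow. The section on removal due to adverse events says: "Participants will be removed from the study following an AE if treating medical team indicate" that walking practice is no longer tolerated.

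**The concern.** A pilot of this kind exists to count the people who do not start, do not finish or cannot be assessed. If the set used for the primary endpoint admits only people who have an assessment, those with none are gone before counting starts. The percentage with complete data rises, and total loss to follow-up is zero by definition. Under the first definition, a participant who never starts treatment, and so has plainly not completed it, also disappears from item (c).

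The ITT label makes this harder to notice, because both definitions exclude randomised participants for what happened after randomisation. The figures affected are those meant to plan the next trial.

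**Working it through.** The Protocol states no completeness or drop-out figure, so there is nothing to reproduce. The contradiction lies in the text; the arithmetic only shows how large the effect could be.

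**Side by side.** Items (c) to (e) stand under the heading Primary endpoint. The population section assigns primary endpoints to the full analysis set. The Synopsis (statistical methods) and the missing-data section promise tabulations but name no denominator. So the only denominator in the Protocol for these items is one that requires a post-baseline assessment.

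**Who leaves the set.**
- No usable post-baseline assessment: removed under both definitions. The removal section adds to this group, because it leaves out measures taken outside a 5-day window.
- Never treated but assessed: removed under the first definition only.
- Stopped treatment and assessed at least once: stays. Table 1 has two post-baseline visits, at 8 weeks and 3 months, and one is enough.

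**Completeness.** Let N = randomised, k = excluded from the set, m = others with some missing values. Assume first that nobody excluded has complete data.
- All randomised: (N − k − m)/N
- Full analysis set: (N − k − m)/(N − k)
- The ratio of the second to the first is N/(N − k).

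N = 60 is from the Synopsis and the randomisation section; every loss below is assumed.
- Milder case: 2 never start, 6 more have no post-baseline gait speed, 6 others are partly missing. k = 8, set = 52, complete = 52 − 6 = 46. 46/60 = 77% against 46/52 = 88%.
- Heavier case: 3, 9 and 6. k = 12, set = 48, complete = 42. 42/60 = 70% against 42/48 = 87.5%.
- Heavier case under each definition, if the 3 who never start are nevertheless fully assessed: 45/60 = 75% over all randomised, 42/48 = 87.5% under the first definition, 45/51 = 88.2% under the second.
- Milder case with N = 50, the number in the sample-size section: 36/50 = 72% against 36/42 = 85.7%.

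**Drop-out, item (c).** Now let k be those with no assessment, all assumed to be non-completers, and m those who stop treatment but are assessed. All randomised: (k + m)/N. Full analysis set: m/(N − k). With N = 60 and m = 3:
- k = 3: 6/60 = 10.0% against 3/57 = 5.3%
- k = 6: 9/60 = 15.0% against 3/54 = 5.6%
- k = 12: 15/60 = 25.0% against 3/48 = 6.3%

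The all-randomised rate rises by 15 percentage points while the set's figure hardly moves.

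**Effect on the next trial's size.** Inflation for missing outcomes is 1/(1 − loss). Suppose those who stop treatment are assessed at both visits, so that the true loss is k/N, but the set's non-completion rate is used instead.
- k = 12, m = 3: true loss 20%, factor 1.25; set figure 6.3%, factor 48/45 = 1.07. Too small.
- k = 3, m = 6: true loss 5%, factor 60/57 = 1.05; set figure 6/57 = 10.5%, factor 57/51 = 1.12. Too large.

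Exclusion from the set and treating non-completion as attrition pull in opposite directions, so the net effect on sample size is not determined.

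**The case against.** The strongest reply is that the set was never meant for the feasibility items. Recruitment, therapist willingness and reasons for drop-out have no post-baseline assessment, whereas gait speed does, and the treatment section calls recovery of walking the primary outcome. Other text also points to counting the people lost: withdrawn participants are not replaced because non-completion is to be counted, and missing data are to be tabulated with reasons. Further detail is left to a separate SAP. This reading is plausible and it stands as a possibility. But the population section does not say it, and the section headed Primary endpoint puts the feasibility items first. Even on this reading, the two definitions conflict and neither is all-randomised.

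Some stronger readings are tempting but not supported.
- A reader might infer that all drop-outs vanish and the drop-out figure becomes zero. It does not: those who stop treatment and are assessed once remain, and their other missing visit stays visible.
- A reader might infer that the definitive trial will certainly be undersized. The direction is open, as shown.
- A reader might take the remark that "participants may not then receive the experimental intervention as planned" as a forecast of untreated participants. The trial management section lists it as a medium-level risk tied to funding.
- The Synopsis plan to "tabulate the number and percentage of patients who are invited to participate, and who are recruited, into each arm of the trial" might be read as tabulating invitations by arm, although invitation precedes allocation. The arm can equally attach to recruitment alone, and nothing here depends on it.

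**Conclusion.** The point holds as an error of wording with real consequences if followed. The Protocol assigns its primary endpoints to a set that, under both definitions, excludes randomised participants with no usable post-baseline assessment, and under the first also those never treated. It calls this set ITT, which it is not.

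For people with no assessment the direction is clear: completeness is overstated by the factor N/(N − k), and complete loss cannot be seen. The illustrations give overstatements of about 12 percentage points (77% to 88%) and 17.5 points (70% to 87.5%). They rest wholly on assumed losses, since the Protocol gives no expected rate. The documents do not show that the authors intended to discard these people; they show that the text, as it stands, tells the analyst to do so.

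Separately, three sections differ on whether leaving treatment means leaving the study. Until they are reconciled, item (c) has no single meaning.

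**What to change.** In Definition of population analysed:
1. Make all randomised participants, by allocated arm, the denominator for items (c) to (e).
2. Give one definition of the observed-outcome set, restrict it to describing the clinical outcomes (gait and the secondary measures), and do not call it ITT. If this was always the intent, say so.

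In Primary endpoint:

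3. Report non-completion of treatment separately from missing outcomes at 8 weeks and at 3 months, and use the missing-outcome rate to inflate the definitive trial's sample size.

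The Primary endpoint section and the sections on removal from therapy and removal after adverse events must also be reconciled on whether leaving treatment means leaving the study. That decision belongs to the investigators.

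The cost is a few sentences and matching wording in the SAP. No new data are needed. The only drawback is that reported completeness will look less favourable.
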